#### Quantitative primary data analysis (survey).

Initially, descriptive statistics (frequencies, means, medians, and standard deviations) will be used to characterize the sample profile. Subsequently, to operate key concepts, composite indices will be constructed, and their internal consistency will be assessed using Cronbach’s alpha (α > 0.7) and/or Confirmatory Factor Analysis (CFA) [43]. The planned indices include Income and Livelihood Diversification Index (ILDI); Climate Adaptation Practices Index (CAPI); Bioeconomy Engagement Index (BEI); and Climate Vulnerability Perception Scale (CVPS).

To test the hypotheses in Table 1, linear mixed-effects models (LMM) and generalized linear mixed-effects models (GLMM) [44] will be applied, which are appropriate for hierarchical data (families nested within settlements and municipalities). The MCVI and the municipal engagement typology will be included as higher-level variables (level 2), while family characteristics (level 1) will be used as predictors and control variables.

#### Addressing confounding and sensitivity analysis.

To mitigate potential confounding, the multilevel models will include a rich set of pre-specified covariates at different levels: (1) Household Level (Level 1): Age and education of the household head, household size, gender of the household head, asset index, length of residence in the settlement; (2) Settlement Level (Level 2): Settlement type, distance to the nearest paved road, presence of a producers’ cooperative, years since settlement establishment; (3) Municipality Level (Level 3): Municipal Climate Vulnerability Index (MCVI), Municipal Climate Engagement Typology, and geographic region (e.g., floodplain vs. upland).

Acknowledging the impossibility of measuring all potential confounders, we will conduct a formal sensitivity analysis for the key associations related to our primary hypotheses (e.g., the association between BEI and household income). We will use the sensemakr package in R, following the framework developed by Cinelli and Hazlett (2025) [45]. For each key finding, we will report the Robustness Value (RV), the minimum strength of association (partial $R^{\text{2}}$) that an unmeasured confounder would need to have with both the exposure and the outcome to explain away the observed effect. We will also present contour plots to visualize how the effect estimate and its confidence interval would change under different scenarios of confounding. This will provide readers with a transparent assessment of the robustness of our inferences to unobserved confounding.

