Income and Livelihood Diversification Index (ILDI): a continuous score (0–1) that synthesizes the distribution of agricultural, extractive, and non-agricultural income. This index is adapted from standard diversification measures widely used in livelihood and rural development research (e.g., Herfindahl–Hirschman approaches [30]). *Expected direction*: higher values will be associated with greater diversification of adaptation actions (PH2).Climate Vulnerability Perception Scale (CVPS): a reflective scale (1–5) constructed from Likert-type items assessing perceived frequency, severity, and impacts of climate-related events. This scale is adapted conceptually from prior work on climate risk perception but operationalized specifically for Amazonian rural contexts. Internal consistency and dimensionality will be assessed through Cronbach’s alpha [31] and confirmatory factor analysis. *Expected direction*: lower perceived vulnerability in settlements with greater forest cover and ecological connectivity (PH1).Bioeconomy Engagement Index (BEI): an ordinal variable (level 0 = no engagement; 1 = primary production; 2 = processing; 3 = processing + certification). This is an original indicator developed by the authors, grounded in literature on value-chain upgrading and socio-bioeconomy transitions. *Expected direction*: Higher values reflect greater involvement in bioeconomy value chains. This indicator will be used to examine whether higher engagement is associated with household income and with adoption of adaptation and mitigation practices (PH5).Reported Adaptive Capacity Index (RACI): a reflective score derived from farmers’ self-assessment of their ability to respond to climate impacts. The index is constructed as the average of Likert-scale items (range 1–5), where higher values indicate greater perceived adaptive capacity. Items draw on established adaptation assessment frameworks but were adapted to the Amazonian rural context. This indicator is used to examine associations proposed inPH4.

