#### Data collection methods.

The study employs three complementary data collection methods: household surveys, semi-structured interviews, and focus groups. The household survey captures quantitative information on socioeconomic characteristics, productive activities, climate perceptions, and adaptation practices, using a structured questionnaire administered face-to-face to a randomly selected adult decision-maker in each household.

Qualitative data will be collected through two instruments. First, semi-structured interviews will be conducted with municipal public managers (1–3 per municipality), allowing in-depth exploration of policy implementation challenges, resource constraints, and perceptions of local climate risks. Second, focus groups with community leaders (8–12 participants per settlement) will be used to capture collective experiences, shared vulnerabilities, and community-level adaptation strategies. Both methods are designed to generate rich contextual information that complements survey findings.

Detailed guides for each instrument (survey, interview, and focus group) are provided in the Supplementary Material (S1–S3 Files).

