#### Participant characteristics.

Participants include: (i) local public managers (1–3 per municipality), responsible for municipal policies on agriculture, environment, or rural development; (ii) community leaders (8–12 per settlement), invited to participate in focus groups, representing different social and productive segments; and (iii) settled families (up to 50 per settlement), covering a diversity of socioeconomic, productive, and demographic profiles. The study expects to include family farmers across different age groups, education levels, family compositions, and modes of engagement in local markets, as well as varying degrees of dependence on natural resources and participation in public policies. In each household, the respondent will be the adult member primarily responsible for agricultural and livelihood decisions (typically the main decision-maker), as this person is expected to have the most comprehensive knowledge of production, income sources, and climate-related impacts.

This sampling strategy seeks to balance territorial representativeness, social diversity, and logistical feasibility, enabling comparisons across municipalities, settlement types, and family profiles.

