#### Selection of families.

In each selected settlement, up to 50 families will participate in the study, chosen through simple random sampling from official lists provided by local associations or INCRA. The inclusion criteria for families are: (i) residing in the settlement; and (ii) having an adult household member available to respond to the questionnaire; and (iii) providing voluntary informed consent (ICF). Families will be excluded if: (i) they do not meet the residency requirement; (ii) they refuse or cannot provide consent; or (iii) communication barriers make the interview unfeasible.

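### CVPS and RACI are one respondent's own ratings, but the person-level demographic covariates describe the household head, whom no respondent rule requires to be the person interviewed

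*Protocol article*

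**What the plan says.** All references are to the Protocol article.

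- **Covariates** (Addressing confounding and sensitivity analysis): "the multilevel models will include a rich set of pre-specified covariates at different levels". The demographic ones at household level are "Age and education of the household head, household size, gender of the household head". The asset index and length of residence complete that level. No separate list is given for the perception outcomes, and neither the respondent's age, sex and education nor the respondent's relation to the head is listed.
- **Outcomes** (Primary and secondary outcomes): CVPS is "constructed from Likert-type items assessing perceived frequency, severity, and impacts of climate-related events". RACI is "a reflective score derived from farmers’ self-assessment of their ability to respond to climate impacts". Both are primary; CVPS is linked to PH1 and RACI to PH4. The same section also uses RACI for PH3, on multigenerational composition and membership of community organizations.
- **Respondent**: Data collection methods has the survey done "using a structured questionnaire administered face-to-face to a randomly selected adult decision-maker in each household". Participant characteristics says "the respondent will be the adult member primarily responsible for agricultural and livelihood decisions". Selection of families asks only for "having an adult household member available to respond to the questionnaire".

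**The concern.** A rating on a perception scale depends on who gives it. Adjusting such a rating for age, sex and education makes sense when these belong to the rater. The plan adjusts for the head's, and nothing in the article makes the rater the head.

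Two things are at stake. First, the demographic covariates explain less of the variation in CVPS and RACI than they could. Second, if the mix of respondents differs along an exposure, part of that difference stays in the estimated association. The most direct route is PH3 on RACI: a household with several generations plausibly has more adults who could answer, so the exposure itself may change who is interviewed. For PH1 and PH4 the exposures sit at settlement and municipality level, so bias needs the respondent mix to vary with forest cover or municipal policy.

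**Working it through.** **1. Can respondent and head differ?** Set the three descriptions against the covariate line.

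- Random selection among adult decision-makers: yes. If the head is one of k such adults, the respondent is the head with probability 1/k, which is 50% for k = 2 and 33% for k = 3. If multigenerational households had three and others two (an assumption), coincidence would differ by 17 points along the PH3 exposure.
- The adult mainly responsible for decisions: less often. If the head were defined as that adult, the two would be the same person.
- Any available adult: yes. This is an eligibility condition rather than a selection rule, but it does not bring in the head either.

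**2. How much does the head's sex stand in for the respondent's?** The article gives no coincidence rate, so this is an illustration. Assume 80% male heads, with the respondent being the head with probability c and otherwise an opposite-sex partner. At c = 0.9:

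- male respondent share = 0.8 × 0.9 + 0.2 × 0.1 = 0.74, variance 0.74 × 0.26 = 0.1924
- variance left once head sex is known = 0.9 × 0.1 = 0.09
- share accounted for = 1 − 0.09/0.1924 = 53%

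A least-squares simulation (1,000,000 households; respondent sex shifts a household-level exposure and the rating by 0.4 each; residual SD 1; true exposure effect 0) gives the share of respondent-sex confounding removed by head sex:

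| c | removed by head sex |
|---|---|
| 1.0 | all, up to simulation error (95% printed) |
| 0.9 | 51% |
| 0.8 | 25% |
| 0.7 | 10% |
| 0.5 | 0% |

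The respondent's own sex removes essentially all of it in every row. Because the exposure is at household level, this speaks to PH3, not to PH1 or PH4.

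**3. The yardstick.** Table 2 gives a minimum detectable effect of 0.34 for a continuous outcome at ICC 0.05 with 600 families in 30 settlements. An approximate check with half the settlements in each group: design effect 1 + 19 × 0.05 = 1.95; SE = √(4 × 1.95/600) = 0.114; multiplied by the t quantiles on 28 degrees of freedom (2.048 + 0.855) this gives 0.331, close to 0.34. The figure can therefore be read as a between-settlement difference in SD units. It does not depend on the covariate list.

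**4. Size for a between-settlement contrast.** Shift = rating gap between the sexes × difference in female respondent share that remains after adjustment for head sex. Both inputs are assumptions.

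- 10 points: 0.2 × 0.10 = 0.02 and 0.3 × 0.10 = 0.03 SD; 0.02/0.34 = 6%, 0.03/0.34 = 9%.
- 20–30 points: 0.2 × 0.20 = 0.04 and 0.3 × 0.30 = 0.09 SD; 0.04/0.34 = 12%, 0.09/0.34 = 26%.

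In the two-person setting of step 2, the remaining difference cannot exceed the between-group difference in how often respondent and head differ. If they differ in at most 10% of households everywhere, the shift is at most 0.10 × 0.3 = 0.03 SD. The second line needs that rate to differ by at least 20–30 points between settlement groups, so it is a strong case.

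**The case against.** The best counter-argument is that the head is simply the main decision-maker. If the study defines the head that way and applies the rule in Participant characteristics, respondent and head coincide and the problem largely goes. That stands as a condition: a reader might infer that the mismatch persists whichever respondent rule is adopted, and the article does not support that. It does not dispose of the point, because the article neither gives that definition nor withdraws the random selection in Data collection methods.

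Second, the questionnaire (S1 File) is not shown and may already record respondent traits. True, but the covariate list is a stated choice and would still need to change.

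Third, head traits are not simply irrelevant. CVPS items touch crop loss and food insecurity, which are household matters, and the head's age may confound PH3. A reader might conclude that the head's traits should be taken out of the RACI and CVPS models; nothing in the article shows that this would be better.

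Fourth, a reader might take PH1 and PH4 to be biased as planned. The article says nothing about respondent mix by forest cover or policy, so this is only a possibility. The precision loss is also limited for these contrasts, since the article states that power depends mainly on the number of settlements.

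Finally, the planned robustness values show how strong an omitted trait would have to be. They do not adjust for a trait that can be recorded at interview.

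**Conclusion.** The mismatch is real on the face of the article: self-ratings by an adult who need not be the head, adjusted for the head's age, education and gender. It is likely to occur under random selection of the respondent and less so if the main decision-maker answers. The consequence is partial, not absent, adjustment for the respondent's traits, with some loss of precision and a possible bias that is most direct for RACI under PH3.

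The actual size cannot be derived from the article. Under the assumed rating gap and a remaining 10-point difference in female respondent share it is 0.02–0.03 SD, 6–9% of 0.34. The range 0.04–0.09 SD (12–26%) should not be quoted as the expected effect. The point is limited to CVPS and RACI; head traits are reasonable for household outcomes such as ILDI and income. It is worth correcting because the correction is cheap and respondent traits are hard to recover after fieldwork.

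**What to change.** 1. Reconcile the three descriptions of the respondent in Data collection methods, Participant characteristics and Selection of families, and define the household head.
2. Record the respondent's age, sex, education and relation to the head at interview, if S1 File does not already do so. Fieldwork is scheduled from December 2025 to December 2026.
3. In every CVPS and RACI model, add the respondent's age, sex and education and a yes/no term for respondent is head. Add these to the head's traits rather than substituting them, so that the head's age stays available for PH3.
4. Leave the head's traits as they are for household outcomes.
5. Report how often respondent and head coincide, overall and by the PH1, PH3 and PH4 exposures.

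The cost is a few questionnaire fields at most and a few extra household-level coefficients among 600 or more families. Respondent and head traits will be collinear where the two people usually coincide. That makes their separate coefficients imprecise, but these are adjustment terms and not the associations under test. If the two always coincide, the added terms are redundant and drop out.

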The choice of 15 municipalities is not arbitrary but rather designed to capture the diverse socioecological contexts of agrarian reform settlements in Pará. These municipalities encompass distinct territorial and economic features that are central to understanding adaptation dynamics in the Amazon. They include: (i) areas strongly influenced by mining activities, where extractive industries create both opportunities and vulnerabilities; (ii) regions dominated by agribusiness expansion, with intensive land-use change and pressure on family farming; (iii) floodplain and dryland environments, which present contrasting climate risks and livelihood strategies; (iv) municipalities intersected by major highways such as the Transamazon Highway, where infrastructure development shapes access to markets and exposure to environmental impacts; and (v) extractive and conservation-oriented settlements, where socio-biodiversity chains and traditional livelihoods play a central role.

By sampling across this range of contexts, the study captures key socioecological environments characteristic of Amazonian rural settlements. The selection is not numerically balanced across all contexts; rather, municipalities were purposively chosen to ensure representation of major settlement types and territorial dynamics relevant to climate adaptation. This approach enhances analytical robustness and supports the transferability of findings.

In each selected municipality, up to two agrarian reform settlements will be sampled, ensuring representation of the main settlement modalities nationally recognized. This approach will enable a robust comparative analysis of how different institutional designs and production bases mediate community vulnerability and adaptive capacity in the face of climate change.

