#### Qualitative saturation criterion.

Qualitative data collection will follow the principle of theoretical saturation [37], assessed iteratively by the analysis team during coding. As a guiding strategy, we will consider saturation reached when two or more consecutive interviews or focus groups no longer generate new relevant codes. However, given the high heterogeneity of Amazonian settlements (e.g., floodplains, mining zones, forest-based communities), this criterion will be applied flexibly. Data collection may be extended in specific contexts if new themes continue to emerge or if settlement-specific dynamics require further exploration. To ensure robustness, saturation will be evaluated both within settlement types and across municipalities and will be triangulated with survey findings and field observations to confirm completeness.

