#### Post-pilot methodological adjustments.

Testing the instruments in Marabá (PA) resulted in crucial refinements. For Phase 1, the policy and budget analysis methodology was expanded to systematically capture implicit climate actions, as the pilot revealed that most municipal climate responses are driven by sectoral policies (e.g., agriculture, infrastructure) not explicitly labeled as climate related. For Phase 2, the household survey was adapted to include specific modules for riverine and floodplain communities, capturing climate impacts (e.g., changes in flood cycles, river-based access). The interview guide with managers was revised to replace technical jargon with more accessible terms, reflecting the fact that many municipalities lack a consolidated formal framework for climate policy.

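### Floodplain versus upland is entered only at municipality level; if the two settlements sampled in a municipality differ, one is miscoded and the difference is left unadjusted for PH1

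*Protocol article*

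**What the plan says.** The section Addressing confounding and sensitivity analysis assigns each pre-specified covariate to a level. For municipalities (Level 3) it lists the MCVI, the engagement typology and "geographic region (e.g., floodplain vs. upland". The settlement list begins "2) Settlement Level (Level 2): Settlement type, distance to the nearest paved road" and adds only presence of a cooperative and settlement age. It contains no flood or hazard setting.

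Other sections use the same attribute as follows:

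- Qualitative saturation criterion, about settlements: "given the high heterogeneity of Amazonian settlements (e.g., floodplains, mining zones, forest-based communities".
- Post-pilot methodological adjustments, about communities: "the household survey was adapted to include specific modules for riverine and floodplain communities".
- Sample, inclusion and exclusion criteria, and participant characteristics, in a list of contexts that the 15 municipalities cover: "floodplain and dryland environments, which present contrasting climate risks and livelihood strategies".

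The last section also sets the sampling within municipalities: "In each selected municipality, up to two agrarian reform settlements will be sampled". No section lists the settlements, says whether any municipality holds both settings, or says how such a municipality would be coded.

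**The concern.** A Level 3 covariate has one value per municipality, so two settlements in the same municipality necessarily share it. If flood setting varies between them, the model cannot see the variation.

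PH1 is where this counts. Its exposure, forest cover and ecological connectivity, is defined for settlements. Its linked primary outcome, the CVPS, averages perception items that include flood. The article itself says that floodplain and dryland settings carry contrasting risks and livelihoods. Flood setting therefore bears on the outcome and may plausibly be related to the exposure, which makes it a candidate confounder at the level where the exposure varies. The hazard information that the model does hold (region, and the climate exposure part of the MCVI) all sits one level higher.

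**Working it through.** The article gives no figure that depends on the level of this covariate, so there is nothing to reproduce. The check compares the levels used in the text and then counts what a municipal value can get wrong.

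**1. Levels used in the text**

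| Section | Flood setting is attached to |
|---|---|
| Addressing confounding and sensitivity analysis | municipality (Level 3) |
| Sample, inclusion and exclusion criteria, and participant characteristics | municipalities, as a context for their selection |
| Qualitative saturation criterion | settlements |
| Post-pilot methodological adjustments | communities |

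The attribute is used at both levels, but the model takes it only at the higher one.

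**2. Settlements miscoded**

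Inputs: 15 municipalities and up to 30 settlements (Sample justification and statistical power), so two per municipality at the maximum. Let m be the number of municipalities with one floodplain and one upland settlement. The article does not give m. With one binary value per municipality, each mixed municipality miscodes exactly one settlement:

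miscoded share = m / 30.

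**3. Variation that a municipal covariate cannot reach**

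Code floodplain 1 and upland 0. Each mixed pair contributes 2 × 0.5² = 0.5 to the within-municipality sum of squares, so that sum is m/2. The total is 30·p·(1 − p), where p is the proportion of floodplain settlements. Assume that the unmixed municipalities are split as evenly as possible. Then p is 1/2, or 14/30 when their number is odd, as at m = 8. With p = 1/2 the total is 7.5 and the within share is (m/2)/7.5 = m/15. At m = 8 the total is 30 × (14/30) × (16/30) = 7.467, and the share is 4/7.467.

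| m (assumed) | miscoded of 30 | share miscoded | within-municipality share of variation |
|---|---|---|---|
| 0 | 0 | 0% | 0% |
| 1 | 1 | 3.3% | 6.7% |
| 3 | 3 | 10% | 20% |
| 5 | 5 | 16.7% | 33.3% |
| 8 | 8 | 26.7% | 53.6% |
| 15 | 15 | 50% | 100% |

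The rows span the whole possible range, and the article gives no reason to favour any of them. A separate mixed category at municipality level would avoid a false label, but the last column would not change, because both settlements would still share one value.

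**4. Effect on PH1**

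To first order, the bias in the PH1 coefficient from the unadjusted part is γ × δ. Here γ is the effect of flood setting on the CVPS, and δ is the slope of flood setting on forest cover among settlements, given the covariates in the model. The article gives neither, so the bias cannot be sized. It is zero if m = 0. Random intercepts do not remove it: a municipality intercept is common to both settlements, and a settlement intercept absorbs residual variance without adjusting for a confounder at that same level.

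**5. Coding per settlement**

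If m = 0, the settlement-level column is identical to the municipal one and the fitted model is the same. If m > 0, miscoding falls from m to 0.

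**The case against.** The strongest reply is that no mixed municipality is shown. The description of the sample lists floodplain and dryland among the contexts that the municipalities cover, which agrees with the Level 3 placement. Two settlements are taken so that the main settlement modalities are represented, and the article links settlement types to tenure and institutional arrangements, not to hydrology. Different modalities therefore do not imply different flood settings. Eligible settlements must also be typical of their municipality in production and socioeconomic terms, which makes contrasting pairs less likely. All of this stands. A reader might infer that settlements will be given the wrong setting. The article does not support that, and zero miscoded settlements is compatible with its text.

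Second, the wording of the covariate is only an example, and a condensed article may leave coding rules to a fuller document. This stands for the categories but not for the level, which is explicit.

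Third, settlement type, road distance and cooperative presence may absorb part of the difference, and a formal sensitivity analysis for unmeasured confounding is planned. Both may limit the harm. The article does not say that settlement type captures flood setting, however, and a sensitivity analysis is a weak substitute for adjusting for something that can simply be recorded.

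A reader might also infer that moving the term down frees a degree of freedom for PH4 among the 15 municipalities. With an intercept (15 − 1 = 14), MCVI (1), the three-class typology (2) and a two-class region (1) leave 14 − 4 = 10. Dropping region leaves 11, but replacing it with the three superintendencies (2) leaves 14 − 5 = 9. A settlement-level variable that differs mainly between municipalities would also still compete for the same between-municipality information. The change should not be justified on that ground.

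**Conclusion.** The point holds as a conditional weakness in the covariate specification. Flood setting is fixed at municipality level, no settlement-level covariate captures it, and the article elsewhere treats it as something that distinguishes settlements or communities. Where paired settlements differ, one is miscoded and the within-municipality difference stays unadjusted for PH1.

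The size is unknown: 0 to 15 of 30 settlements, taking two per municipality and a two-class covariate. The share of flood-setting variation out of reach runs from 0% to 100% over the same range, with the intermediate values resting on a near-even split of settings. Any bias in PH1 further requires that setting affects the CVPS and is related to forest cover; the first is plausible from the article and the second is not shown. This is a low-cost improvement, not an established error in the results to come.

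**What to change.** In Addressing confounding and sensitivity analysis, move floodplain versus upland from the Level 3 list to the Level 2 list, with one value recorded per settlement. Make the sections on sample selection, saturation and post-pilot changes consistent with that level.

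The cost is recording one setting per settlement, at most 30 values. The "specific modules for riverine and floodplain communities" suggest that the field team will often know the setting already, but the article does not say whether modules are assigned by settlement or by household, so the item should be recorded explicitly. Fieldwork is scheduled from December 2025 to December 2026 and analysis for 2027. The covariate list should be amended before outcomes are analysed.
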